### **7.11 Premature termination of the study**

Only in case of logistical reasons the EU-CaRE consortium (steering committee) can decide to end the study prematurely.

## **8. SAFETY**

### **8.1 Section 10 WMO event**

In accordance to section 10, subsection 1, of the WMO, the site investigator will inform the subjects and the reviewing accredited METC if anything occurs, on the basis of which it appears that the disadvantages of participation may be significantly greater than was foreseen in the research proposal. The study will be suspended pending further review by the accredited METC, except insofar as suspension would jeopardise the subjects' health. The site investigator will take care that all subjects are kept informed.

### **8.2 AEs, SAEs and SUSARs**

#### **8.2.1 Adverse events (AEs)**

Adverse events are defined as any undesirable experience occurring to a subject during the study, whether or not considered related to the experimental intervention. All adverse events reported spontaneously by the subject or observed by the site investigator or his staff will be recorded.

#### **8.2.2 Serious adverse events (SAEs)**

A SAE is any untoward medical occurrence or effect that at any dose:

- results in death;
- is life threatening (at the time of the event);
- requires hospitalisation or prolongation of existing inpatients' hospitalisation;
- results in persistent or significant disability or incapacity;
- is a congenital anomaly or birth defect;
- Any other important medical event that may not result in death, be life threatening, or require hospitalisation, may be considered a serious adverse experience when, based upon appropriate medical judgement, the event may jeopardise the subject or may require an intervention to prevent one of the outcomes listed above.

### **8.2.3 Adverse event reporting**

#### **8.2.3.1 Adverse event monitoring**

The site investigator will monitor the occurrence of AEs for each subject during the course of the study. All AEs reported by the subject, observed by the site investigator, or documented in medical records will be recorded on the AE sheet in the e-CRF, whether believed by the site investigator to be related or unrelated to the study. Starting with the study enrolment, any new event/experience that was not present at T0, or worsening of an event presents at T0, is considered an AE. AEs will not be followed up on once patients finish the study after 12 months. Unchanged, chronic conditions are not AEs and should not be recorded on the AE sheet in the e-CRF. SAEs will be collected and monitored throughout the entire course of the study.

#### **8.2.3.2 Reporting to CRO and/or IRB/MEC/HREC**

Each AE or complication meeting the definition for SAE will be reported upon discovery to the Clinical Research Organization (CRO), preferably within 24 hours of the site investigator's knowledge of the event. The site investigator will further report the event annually to its own institution. The subject's course must be monitored until the event has subsided or, in a case of permanent impairment, until the event stabilises and the overall clinical outcome has been ascertained.

### **8.2.4 Suspected Unexpected Serious Adverse Reactions (SUSARs)**

SUSARs are not expected to occur to a subject during this study.

## **8.3 CLINICAL EVENT COMMITTEE**

The Clinical Event Committee (CEC) will review and adjudicate all clinical endpoint events. The role, membership and meeting schedule of the CEC together with a definition and procedure of the endpoints to be reviewed will be stated in a separate document.

## 9. STATISTICAL ANALYSIS

### 9.1 Statistics

The study parameters are continuous and categorical variables. Categorical variables will be summarised by frequency and percentages. Continuous variables will be summarised by mean and standard deviation (sd) as well as median and interquartile range (IQR). The study parameters will be presented by centre, by intervention group and by time point (baseline, 6 months and 12 months follow-up).

We will describe the differences in outcomes over time between intervention groups in tables and graphs. All endpoints will be analysed for effects related to the intervention (T1) and sustainable effect (T2). Dropout and levels of compliance will be computed and presented as a total, by centre and by intervention group. (Costs of) health care utilisation will be described by centre, by intervention group and by visit. Scores on the self-report validated questionnaire will be coded and summarised according to the corresponding manuals.

The primary treatment comparison is *mCR* group versus control group. Student's t-tests will be used to examine whether the continuous variables are different between the intervention groups at 6 months and at 12 months. When necessary the continuous variables will be transformed to obtain a normal distribution, or a non-parametric test will be used. X2 tests or Fisher's exact tests as appropriate will be used to examine whether the categorical variables are different between the intervention groups at 6 months and at 12 months. A two-sided p-value of less than 0.05 will be considered to be statistically significant in all analyses.

Statistical analyses will be performed in SPSS and SAS. The statistical analyses will be described in detail in the Statistical Analysis Plan.

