### 3. OBJECTIVES

Objectives:

- To assess whether *mCR* programmes result in better sustained effects on physical, mental and social outcomes in elderly patients not opting for regular CR, than patients who do not follow the *mCR* programme.
- To assess whether *mCR* as alternative for a regular CR programme is an effective means to increase participation and adherence of elderly in a CR programme.
- To analyse the induced costs of the *mCR* programme and determine its cost effectiveness.

Main outcomes include:

- Physical fitness: difference in  $VO_{2peak}$  (T1-T0), (T2-T0) and (T2-T1)
- Traditional risk factors for CVD
- MACE
- General health
- Care utilisation
- Costs of care utilisation
- Adherence
- Compliance

The primary hypothesis of the study is that joining the *mCR* programme results in a greater difference in  $VO_{2peak}$  in cardiac patients between T1-T0 and T2-T0 than not joining the *mCR* programme.

The second hypothesis of the study is that joining the *mCR* programme results in an equal or greater difference in  $VO_{2peak}$  in cardiac patients between T2 and T1 than not joining the *mCR* programme.

The third hypothesis of the study is that the joining the *mCR* programme results in improved traditional risk profile (i.e. lipid profile, HbA1C, lean body mass, blood pressure) in cardiac patients in comparison to not joining the *mCR* programme after 6 (T1) and 12 months (T2).

The fourth hypothesis of the study is that the overall occurrence of MACE (cardiovascular mortality, all-cause mortality, near sudden cardiac death, acute coronary syndrome, CV

intervention/surgery, CV hospital admission, CV emergency visit) in the intervention group is lower than in the control group after T1 and T2.

The fifth hypothesis of the study is that joining the *mCR* programme results in an improved general health (e.g. quality of life (SF-36v2: Physical and Mental Component Summary Score), level of depression (PHQ-9), level of anxiety (GAD-7) and dietary pattern (Mediterranean Diet Score)) in comparison to not joining the *mCR* programme after T1 and T2 in cardiac patients.

The sixth hypothesis of the study is that utilisation of care in the intervention group is lower than in the control group throughout the study period.

The seventh hypothesis of the study is that the costs of care utilisation in the intervention group are lower than in the control group throughout the study period.

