We will test for differences in hazard rates between the *mCR* and control group using Cox regression analysis allowing the baseline hazard functions to differ between centres.

A two-sided p-value of less than 0.05 will be considered to be statistically significant in all univariate analyses.

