## 2. Study objectives

The randomised study has eight objectives.

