#### 4.8 Subgroups

The following important demographic or baseline value defined subgroups are to be analysed for different effects.

- Age
- Gender
- Index event: CAD versus VHR
- Educational attainment: low versus medium/high
- Per protocol: yes versus no

Subgroup analyses will be exploratory.

[figure not shown]

## 5. Study objective 1

Joining the *mCR* programme results in a lesser loss or greater gain in  $VO_{2peak}$  in cardiac patients between T1-T0 and T2-T0 than not joining the *mCR* programme. Primary study endpoint is physical fitness.

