Additionally, we will perform a mixed models repeated measures (MMRM) analysis with intervention effect and time points as fixed effect and centre as random effect and baseline value as covariate. When necessary the outcome variables will be transformed to obtain a normal distribution. The null hypothesis is that the outcome under study is the same at all-time points (T0, T1 and T2). The alternative hypothesis is that the outcome under study at least one of the time points differs from the others. A covariance structure will be selected from several plausible structures. The covariance matrix resulting in the lowest BIC fit statistic will be chosen. We will test for the interaction between intervention group and time in order to investigate whether the development of study parameters over time differs between the interventions. A two-sided p-value of less than 0.05 for will be considered to be statistically significant. If the results of the MMRM analysis are statistically significant, we will run post hoc tests to highlight where these differences occur, adjusting the p value for multiple comparisons using the Tukey procedure.

[figure not shown]

## 7. Study objective 3

Joining the *mCR* programme results in improved traditional risk profile (i.e. lipid profile, HbA1C, lean body mass, blood pressure) in cardiac patients in comparison to not joining the *mCR* programme after 6 (T1) and 12 months (T2).

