### *Outcomes*

#### General Health:

- Changes in Quality of Life: SF-36v2, difference in Physical Component Summary Score and Mental Component Summary Score and 8 domains (T1-T0), (T2-T0)
- Changes in depression score assessed by PHQ-9 questionnaire (T1-T0), (T2-T0)
- Changes in anxiety score assessed by GAD-7 questionnaire (T1-T0), (T2-T0)
- Difference in dietary pattern (reflected by total score) assessed by Mediterranean Diet Score (T1-T0), (T2-T0)

The differences between the randomisation groups on the general health continuous outcomes will follow the same approach as described in section 5 Study objective 1.

[figure not shown]

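### Objectives 1 to 7 are worded as conclusions and every test uses two-sided 0.05, with no testing order across objectives, no exploratory label on secondary endpoints and no deciding test within several objectives

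*Combined protocol and SAP*

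**What the plan says.** **Threshold.** Protocol 9.1: "A two-sided p-value of less than 0.05 will be considered to be statistically significant in all analyses". Protocol 9.3 repeats it at the end of the secondary analyses: "A two-sided p-value of less than 0.05 will be considered to be statistically significant in all univariate analyses".

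**Objectives as conclusions.** SAP section 2 opens with "The randomised study has eight objectives", and objectives 1 to 7 are each a directional statement about mCR. They follow protocol section 3, for example: "The sixth hypothesis of the study is that utilisation of care in the intervention group is lower than in the control group". The primary hypothesis (protocol 3, SAP 2.1) covers VO2peak at both T1-T0 and T2-T0. The primary endpoint (protocol 7.2.1 and 9.2, SAP 5.1) is T1-T0 alone.

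**Multiplicity.** The only adjustment is Tukey, for post hoc comparisons within a significant repeated-measures model of one outcome (protocol 9.3, SAP 6).

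**Labels.** SAP 4.8: "Subgroup analyses will be exploratory". SAP 13.1.3 calls a by-centre participation analysis exploratory, and SAP 18 calls the per-protocol analysis supportive. The secondary endpoints carry neither label.

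**Several tests within one objective.**
- SAP 9 (objective 5) lists the two SF-36 summary scores, eight SF-36 domains, PHQ-9, GAD-7 and the diet score, each at T1-T0 and T2-T0. Protocol 7.2.1 and SAP 2.5 name only the two summary scores from the SF-36.
- SAP 6 (objective 2) specifies a change model and then: "Additionally, we will perform a mixed models repeated measures (MMRM) analysis". SAP 7 (objective 3) uses the same approach.

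**The concern.** Each objective is written as something the trial will conclude, and each p-value is judged against the same threshold. No rule says which result, or how many, would establish an objective. For objective 5 there are 26 comparisons and none is named as deciding. For objectives 2 and 3, two models are fitted to each outcome and the SAP does not say which one stands if they differ. The T2-T0 comparison sits inside the primary hypothesis but outside the primary endpoint, and its order relative to T1-T0 is not stated.

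At stake is how secondary results may be described. An isolated nominal p-value could be presented as an objective met, and the plan would not contradict it. This matters most for the questionnaires: they are self-reported, and protocol 7.5 leaves patient, care provider and outcome assessor unblinded.

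**Working it through.** **The plan's own figure.** The documents state no family-wise error rate and no count of secondary tests. The only related figure is the sample size, which rests on one comparison. With difference 3.0 and SDs 5 and 6, the pooled SD is √((25+36)/2) = 5.52. A two-sided 0.05 t-test then has power 0.799 at 54 per group and 0.806 at 55, which reproduces n=55. The design therefore budgets for one test at 0.05, and that test stays intact.

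**What a false claim for mCR requires.** The tests are two-sided and the objectives are directional, so only the tail favouring mCR counts. That tail is 0.05/2 = 0.025 per test.

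**Formula.** Suppose every null is true and m test statistics share a common correlation ρ. The chance of at least one result favouring mCR is

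P = 1 − ∫ φ(u) · Φ((1.96 − √ρ·u)/√(1−ρ))^m du,

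which at ρ = 0 is 1 − 0.975^m. The documents do not give ρ, so a range is shown.

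**Smallest count, m = 7.** One test for each of hypotheses 2 to 7 (six) plus VO2peak T2-T0 (one).

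| ρ | P | P / 0.025 |
|---|---|---|
| 0 | 1 − 0.975^7 = 0.162 | 6.5 |
| 0.5 | 0.115 | 4.6 |
| 0.8 | 0.074 | 3.0 |

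**Full reconstruction from the SAP, m = 48.** This assumes that the lipid profile means four variables (the lipids in the laboratory list of SAP 13.2), that blood pressure means systolic and diastolic, and that each is tested separately.
- VO2peak T2-T0: 1 (this belongs to objective 1)
- VO2peak T2-T1, change model and repeated-measures model: 2
- Risk factors: (4 lipids + HbA1C + lean body mass + 2 blood pressures) × 2 models = 16
- MACE: 1
- General health: 13 scores × 2 time points = 26
- Care utilisation: 1
- Costs: 1
- Total: 1 + 2 + 16 + 1 + 26 + 1 + 1 = 48

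| ρ | P |
|---|---|
| 0 | 1 − 0.975^48 = 0.70 |
| 0.3 | 0.44 |
| 0.5 | 0.31 |
| 0.8 | 0.15 |

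**A narrower count, m = 30.** Hypotheses 2 to 7 only, no SF-36 domains: T2-T1 (1), eight risk factors × 2 time points (16), five health scores × 2 time points (10), and MACE, utilisation and costs (3). Under independence P = 1 − 0.975^30 = 0.53.

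**Uneven correlation.** Simulation of the 48 tests with assumed correlations of 0.1-0.2 among risk factors, 0.4-0.6 among questionnaires and 0.5-0.7 between T1 and T2, and none between these groups of outcomes, gives 0.52 to 0.63.

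**Not counted.** The t-tests at 6 and 12 months in protocol 9.1 and the per-protocol repeats.

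**The case against.** The other side has real points.

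- The plan does separate primary from secondary. One primary endpoint is named, it alone is powered, and the rest are headed secondary. This stands, and the error rate of the primary test is not in question. But a heading does not say how a secondary p-value may be used, and protocol 9.1 applies one threshold to all of them.
- SAP sections 8 to 11 (objectives 4 to 7) state no threshold, and protocol 9.1 defers detail to the SAP. However, SAP 1.1 names the protocol as its primary source, and SAP 18 lists only the per-protocol set as a change, so the protocol rule carries over.
- The repeated-measures model is introduced as an addition and tests a different null (equality over time and the group-by-time interaction). It may well be meant as secondary to the change model. That is a reasonable reading, and the SAP need only say so.
- Many secondary outcomes are measured rather than self-reported, and protocol 8.3 provides for adjudication of clinical events. The open-label worry therefore applies mainly to the questionnaires.

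Two stronger readings are tempting. A reader might infer that a false finding for mCR is likely, citing 0.61 for 48 tests at correlation 0.5. That figure counts false positives in either direction, including results against mCR; in favour of mCR it is 0.31. With a common correlation, the chance is above one half only when that correlation is low. It also reaches 0.52 to 0.63 under the uneven pattern above, but the documents supply neither the correlations nor the count. A reader might also infer that any single p-value below 0.05 meets an objective. No section says that; the defect is that no section says what does.

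**Conclusion.** The gap is confirmed as one of decision rules and labelling for everything after the primary test. Objectives 1 to 7 are phrased as conclusions and judged at two-sided 0.05 each, with no order or alpha split. The Tukey step does not reach across outcomes, and by the SAP's route it does not reach objective 5 at all, because SAP 9 refers to section 5, which has no such step.

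Even on the smallest count of seven tests, the chance of a false result favouring mCR is about 3 to 6.5 times 0.025. On the reconstruction of about 48 tests it ranges from 0.70 down to 0.15. All these figures assume that mCR affects none of the outcomes counted. The larger count also depends on the lipid and blood pressure assumption. Because the primary analysis is untouched and the remedy is textual, this is a lower-priority SHOULD.

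**What to change.** Amend the SAP, and record the change in SAP section 18 as a departure from protocol 9.1, since the threshold sentence sits in the protocol. State that:

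1. VO2peak T1-T0 is tested first at two-sided 0.05. VO2peak T2-T0 is tested confirmatorily, at the same level, only if T1-T0 is significant. No alpha is taken from the primary test.
2. All other secondary outcomes are exploratory and are reported as estimates with 95% confidence intervals. Their unadjusted p-values are not used to declare an objective met.
3. For objectives 2 and 3 the change model decides and the repeated-measures model is supportive.

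The order fits SAP 4.1, which already analyses T1 before T2 is complete. The text should be fixed before the T1 comparison is seen. SAP section 15 gives the amendment route.

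The cost is a short paragraph and the authors' approval, with no added patients, data or analyses. The downside is that an isolated p-value below 0.05 on a secondary outcome can be reported only as exploratory.

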### 9.2 Primary analyses

The primary endpoint is the change in  $VO_{2peak}$  level between baseline and at 6 months. It will be tested whether this change is different in the *mCR* and the control group by means of linear mixed models with the intervention as a fixed effect. The effect of centre on the outcome is modelled with a random effect. In the analyses we will adjust for the baseline value of  $VO_{2peak}$ . When necessary the outcome variable will be transformed to obtain a normal distribution. The null hypothesis is that there is no difference in mean change in  $VO_{2peak}$  level between the randomised groups. The alternative hypothesis is that the mean

change in  $VO_{2peak}$  level differs between the randomised groups. A two-sided p-value of less than 0.05 will be considered to be statistically significant.

### 9.3 Secondary analyses

#### Sustainable effectiveness

Sustainable effectiveness is defined as a significant improvement in  $VO_{2peak}$  level from baseline (T0) to 12 months after start of CR programme (T2). Differences between intervention groups in sustainable effect will be analysed in similar linear mixed models comparing the difference between change in  $VO_{2peak}$  from T0 to T2 adjusting for baseline values of  $VO_{2peak}$ .

Differences between intervention groups in any of the outcome measures over time will be examined using mixed models repeated measures analysis (MMRM) with intervention group and time points as fixed effects and centre as random effect and baseline values as covariate. When necessary the outcome variables will be transformed to obtain a normal distribution. The null hypothesis is that the outcome under study is the same at all time points (T0, T1 and T2). The alternative hypothesis is that the outcome under study at at least one of the time points differs from the others. We will test for the interaction between intervention and time in order to investigate whether the development of study parameters over time differs between interventions. A two-sided p-value of less than 0.05 for a coefficient will be considered to be statistically significant. If the results of the MMRM analysis are statistically significant, we will run post hoc tests to highlight where these differences occur, adjusting the p-value for multiple comparisons using the Tukey procedure.

Differences between intervention groups in utilisation of medical care will be tested by linear mixed models with centre as random effect for continuous outcome or mixed models for logistic regression for dichotomous outcomes. When necessary continuous outcome variables will be transformed to obtain a normal distribution.

The cumulative incidences of the composite endpoint MACE and the elements from which it is constituted will be presented by intervention group. We will compute the probability of survival free from MACE past given time points (6 months and 1 year) and the survival function will be plotted by intervention group in Kaplan-Meier survival curves. The Kaplan Meier curves will indicate the occurrence of MACE during 1 year of follow-up. Patients who do not experience an event or are lost to follow-up without an event are censored.

We will test for differences in hazard rates between the *mCR* and control group using Cox regression analysis allowing the baseline hazard functions to differ between centres.

A two-sided p-value of less than 0.05 will be considered to be statistically significant in all univariate analyses.

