## **16. Conduct of statistical analysis**

All statistical calculations will be performed using SAS version 9.3 or higher, SPSS version 19 and R version 3.3.1., R Core Team (2016). Statistical analysis will be performed by the beneficiaries Bern, Santiago, Ludwigshafen, Copenhagen and CRO Diagram. Diagram will have an overview of all analyses that will be performed.

Diagram, as reviewing party, will independently reproduce the primary analyses and summary statistics table X, Y, Z. Diagram will explicitly check the code producing tables A, B & C (selected at random) as well as other pieces of code as desired. Each beneficiary is responsible for quality control of all macros and programs used during the analysis.

[figure not shown]

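### Protocol 9.3 judges a two-coefficient intervention-by-time interaction by the p-value of a single coefficient, so the literal rule has a false-positive rate of about 7–10% instead of 5% and depends on an unstated reference visit

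*Combined protocol and SAP*

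**What the plan says.** Protocol section 9.3 plans an MMRM with intervention group and time as fixed effects, with "centre as random effect and baseline values as covariate". The null hypothesis is that "the outcome under study is the same at all time points (T0, T1 and T2"). It then says "We will test for the interaction between intervention and time", and the next sentence gives the criterion: "A two-sided p-value of less than 0.05 for a coefficient will be considered to be statistically significant". A significant MMRM result opens post hoc tests with Tukey adjustment. No joint test, reference visit or coding is named.

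SAP section 6 (study objective 2) carries the same analysis, with the null again stated over all three visits. Its criterion reads "A two-sided p-value of less than 0.05 for will be considered to be statistically significant", with nothing after the preposition. On the within-patient covariance it says "A covariance structure will be selected from several plausible structures", the choice being made by BIC. SAP section 7 applies the section 6 approach to the objective 3 risk factors. SAP section 16 lists the packages: "All statistical calculations will be performed using SAS version 9.3 or higher, SPSS version 19 and R version 3.3.1".

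**The concern.** Two arms and three categorical visits give an interaction with two degrees of freedom, hence two regression coefficients. A rule that accepts *a* coefficient below 0.05 gives two chances to declare that the arms develop differently over time, each at 5%.

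The coefficients also change meaning with the coding. With T0 as reference they are the between-arm differences in T1−T0 and T2−T0. With T2 as reference they compare T0 and T1 with T2, and the on-treatment T1−T0 contrast is not a coefficient at all. The same data can therefore pass under one coding and fail under another.

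At stake is the error rate of the secondary claims about change over time, and of the step that opens the post hoc tests.

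**Working it through.** **Inputs from the documents.** Outcome visits T0, T1, T2 (null hypothesis, protocol 9.3 and SAP 6); two arms, 1:1 (protocol 7.5); 0.05 two-sided per coefficient (protocol 9.3); 83 per arm before the allowance for withdrawal (protocol 5.4, SAP 3). **Assumed:** the correlations between visits. The documents give none, so a range is shown.

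**Step 1: the stated 5%.** It is reproduced by a joint 2-df test (4.97% in 40,000 simulated null trials, 83 per arm, visit correlation 0.8 throughout, compound symmetry true and fitted). It is also reproduced if only one coefficient exists (4.9–5.0%). The per-coefficient rule with two coefficients does not reproduce it.

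**Step 2: bounds for two coefficients.** If each is tested at its proper 5% level, the chance that at least one is significant is at most 0.05 + 0.05 = 10%. If they were independent it would be 1 − 0.95² = 9.75%.

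**Step 3: correlated coefficients.** With equal variances and T0 as reference, the correlation between the two coefficients is

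c = (1 + r12 − r01 − r02) / (2·√[(1 − r01)(1 − r02)]),

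where r01, r02 and r12 are the T0–T1, T0–T2 and T1–T2 correlations. Equal visit correlations r give c = (1 − r)/(2(1 − r)) = 0.5. Correlations 0.5/0.5/0.9 give c = 0.9/(2 × 0.5) = 0.9. The false-positive rate is 1 − P(|Z1| ≤ 1.96 and |Z2| ≤ 1.96), with Z1 and Z2 bivariate normal with correlation c:

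| c | rate |
|---|---|
| 0 | 9.75% |
| 0.5 | 9.07% |
| 0.75 | 8.10% |
| 0.9 | 7.04% |

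**Step 4: reference visit.** Large-sample simulation (4 million draws, covariance known), rates in %:

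| r01 / r02 / r12 | T0 ref. | T1 ref. | T2 ref. | verdict differs, T0 v T2 ref. | joint 2-df |
|---|---|---|---|---|---|
| 0.8 / 0.8 / 0.8 | 9.07 | 9.06 | 9.08 | 6.30 | 5.00 |
| 0.8 / 0.64 / 0.8 | 8.49 | 9.73 | 8.47 | 6.54 | 5.00 |
| 0.7 / 0.6 / 0.85 | 7.86 | 9.74 | 9.06 | 6.47 | 5.00 |
| 0.5 / 0.5 / 0.9 | 7.05 | 9.64 | 9.64 | 6.01 | 5.02 |

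**Step 5: finite sample.** A separate simulation with 83 per arm and 20,000 null trials used visit correlations of 0.7 throughout and of 0.6/0.5/0.75. Either coefficient was significant in 8.2–9.1% of trials and the joint test in 4.9–5.0%. T0- and T2-reference verdicts disagreed in 6.3–6.6%.

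**Limit of the 10% ceiling.** It assumes a correctly specified covariance. If compound symmetry is fitted to the second or third pattern above, the coefficient rule with T0 or T2 reference gives 10.2–12.1% and the joint test 5.7–6.0%. The verdict then changes with the reference in about 2.4–2.5% of trials. The excess over 10% comes from the wrong covariance, not from having two coefficients.

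**The case against.** **A joint test may have been meant.** The plan speaks of one interaction, then of locating differences post hoc with Tukey, which is the usual order of a global test followed by localisation. Protocol 9.1 leaves detail to the SAP, and the SAP sentence no longer mentions a coefficient. This is a fair reading of intent. But the SAP names no joint test and has only an incomplete sentence. SAP 1.1 makes the protocol its primary source, and SAP 18 lists only the per-protocol set as a change. The one complete rule is therefore the protocol's. Tukey adjusts the later comparisons, not the verdict that opens them.

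**Baseline is a covariate.** If T0 were a covariate only, T1 and T2 would be the outcomes, the interaction would have one coefficient and the level would be 5%. This stands as a possibility. The null over three visits, stated in both documents, speaks against it, and the text needs to settle it.

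**The simulations are simpler than the planned model.** They include neither a baseline covariate nor a centre effect. The exact value within the range may shift, but the ceiling in step 2 depends on neither.

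**Stronger readings that a reader might infer:**

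- *An error rate of 12–13%.* Two valid 5% tests cannot reach it. The 20,000-trial simulation gives 11.8–13.1% only if the intervention coefficient at the reference visit is counted too, and that is not part of the interaction.
- *A verdict that changes with the software or the partner.* SAP 16 lists three packages and several analysing parties, but does not say that two of them will analyse the same outcome, and it gives the CRO an overview. The dependence is on the reference visit.
- *Every outcome affected.* In the SAP the MMRM is an additional analysis for VO2peak, extended to the objective 3 risk factors. General health follows section 5, MACE uses Cox regression, and utilisation and costs have their own mixed models.

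**Conclusion.** The point holds for the secondary MMRM analyses. Read literally, with T0, T1 and T2 as outcomes, the rule in protocol 9.3 has a false-positive rate of about 7–10% instead of 5%, and about 6% of null trials change verdict between T0 and T2 reference. These figures rest on assumed visit correlations and a correctly specified covariance. Every pattern tried exceeded 5%.

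Because SAP 6 is incomplete, the defect is an unsafe and unclear rule; it is not shown that the analysis will be run this way. The primary T1−T0 analysis and the separate T2−T0 and T2−T1 change models for VO2peak each test one intervention effect and are untouched. The change should be made, but the primary conclusion does not depend on it.

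**What to change.** In protocol 9.3 and SAP 6:

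1. Replace the coefficient criterion with: *The intervention-by-time interaction is judged by its joint (Type III) F test at the two-sided 5% level, with 2 degrees of freedom when T0, T1 and T2 are outcomes.* In SAP 6 this also completes the broken sentence.
2. State which visits are outcomes, given that baseline is also a covariate. If T0 is a covariate only, the interaction has 1 degree of freedom and concerns T2 versus T1 alone.
3. Report the between-arm T1−T0 and T2−T0 differences as named model contrasts with 95% confidence intervals, and do not use individual regression coefficients to declare significance.

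The cost is a few sentences. No new data are needed, and the joint test is standard output. The downside is that some results that pass under the coefficient rule will no longer pass.
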